### Sample size and power

Sample size calculations were estimated for primary outcomes for a power of 0.8, and a two-tailed p < 0.05. At 1 year, for physical activity, we assume an increase of 300 ± 500 METs-min/sem (intervention, mean ± SD) and 50 ± 400 METs-min/sem for comparison's. A difference effect size (ES) of 0.56 is obtained, for which a sample of 52 participants/group is needed. For changes in body weight (% change of initial) and relative body fat (% change from initial) estimated ES are large (>0.83) and would require considerably less participants/group. Difference ES for some psychosocial variables were also calculated, with estimates (means and SD) based on our previous work [65], and range from 0.67 to 0.83. At maximum, 36 participants/group would be needed to detect significant differences in these variables between intervention and controls. Assuming a dropout rate of 20%, 120 participants/group will remain at 1-year (our primary endpoint), enough to detect even small differences in PA. The lowest ES observed (for PA, ~0.5) would require ~60 participants/group. In the behavioral sciences, "moderate" and "strong" ES for associations between variables (R^2^x100 or percent variance accounted) have been set at 5% and 10% respectively, which is equivalent to correlations of 0.22 and 0.31 [66]. Thus, our sample size will be adequate even for the lowest (i.e., "moderate") association levels.

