## Methods

### Study design

Randomized controlled trial, analyzing 3-year change in primary outcomes, consisting of a 1-year behavior change intervention and a 2-year follow-up period with no intervention. Participants (n = 259) entered the study in 3 annual cohorts and each cohort was split into 2 randomly-assigned groups: one intervention group and one comparison group. The intervention group attended about 30 group sessions for approximately one year. The comparison group received a general health education curriculum based on several 3 to 6-week long educational topics (e.g. preventive nutrition, stress management, self-care and effective communication skills, among others). The Technical University of Lisbon – Faculty of Human Kinetic Ethics Review Board approved the study.

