### Recruitment

#### Inclusion criteria

To be included in the study, participants were required to be female, between 25–50 years old, pre-menopausal, have a BMI between 25 and 40 kg/m^2^, be willing to attend weekly meetings (during 1 year) and be tested regularly (during 3 years); be free from major illnesses, not taking (or having taken in the previous year) medication known to interfere with body weight regulation, namely anti-depressive medication; and willing to not participate in any other formal or informal weight loss program during the first year of the study (intervention group only). Prior to participation, all participants gave written informed consent.

Participants were recruited through a website, newspapers, TV and radio ads, and with flyers distributed in health care centers, local services, schools, etc., asking candidates to enroll in a group-based behavioral (i.e., no medication involved) weight management program. All women who called to inquire about the study were invited to one of several recruitment sessions in which the study was described in more detail, including inclusion/exclusion criteria. Of the 943 women who attended recruitment sessions, 462 were excluded because they failed to comply with the inclusion criteria, primarily related to BMI/age limits; 481 met inclusion criteria but only 290 ultimately committed to the study and were contacted to schedule their baseline measurements; 258 completed initial assessments and entered the study.

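### The 120 women per group said to remain at 1 year after 20% dropout cannot come from the 258 or 259 who entered; about 103 per group would

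*Protocol article*

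**What the plan says.** All of this is in the protocol article.

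- **Sample size and power, retention.** The expected 1-year sample is given as "Assuming a dropout rate of 20%, 120 participants/group will remain at 1-year", with 1 year named as the primary endpoint. The sentence goes on to call this "enough to detect even small differences in PA". No number is attached to small.
- **Sample size and power, inputs.** The calculation is "for a power of 0.8, and a two-tailed p < 0.05". For PA, "we assume an increase of 300 ± 500 METs-min/sem (intervention, mean ± SD") is set against "50 ± 400 METs-min/sem for comparison's". The result is: "A difference effect size (ES) of 0.56 is obtained, for which a sample of 52 participants/group is needed". A lowest effect size of about 0.5 is said to need about 60 per group.
- **Inclusion criteria.** The recruitment account ends with "258 completed initial assessments and entered the study".
- **Study design.** "Participants (n = 259) entered the study in 3 annual cohorts", each divided at random into an intervention and a comparison group. No allocation ratio is given.
- **Statistical analyses.** Two analyses are planned: completers only, and intent-to-treat with missing follow-up scores replaced by baseline values as the default.

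**The concern.** The expected number at the primary endpoint should follow from the number entered and the assumed dropout. The article gives all three figures, and they do not agree. Because recruitment is reported in the past tense as finished, 120 per group cannot be read as a target still to be met. It also matches neither planned analysis: it is too high for completers at 20% loss and too low for an analysis that keeps every entrant.

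Two smaller points belong to the same correction. The number of women who entered has two values, and it is the denominator of the intent-to-treat analysis. The sensitivity claim is attached to the wrong sample size and is unquantified, so a reader cannot tell what PA difference the trial can detect.

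**Working it through.** **Inputs.** Two-sided alpha 0.05, power 0.80, PA changes of 300 ± 500 and 50 ± 400 MET-min/week (the article's 'sem' is read as week), 20% dropout and 120 per group remaining, all from Sample size and power; 258 entrants from Inclusion criteria; 259 from Study design. Assumption: 1:1 allocation for every per-group figure.

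**1. The article's PA calculation reproduces.** The difference is 300 − 50 = 250. With the averaged SD, (500 + 400)/2 = 450, d = 250/450 = 0.556, which needs 52 per group by the two-sample t-test, as stated. With the root-mean-square SD, √((500² + 400²)/2) = 452.8, d = 0.552 and 53 per group are needed. An effect of 0.5 needs 63 to 64, close to the stated 60 or so.

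**2. The retained number does not reproduce.** Remaining = entrants × (1 − 0.20).

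| Starting number | Remaining in total | Per group at 1:1 |
|---|---|---|
| 258 (Inclusion criteria) | 206.4 | 103.2 |
| 259 (Study design) | 207.2 | 103.6 |
| 290 (committed before baseline) | 232.0 | 116.0 |
| 300 (not in the article) | 240.0 | 120.0 |

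Working backwards, 120/0.80 = 150 per group, or 300 entrants. The common shortcut of multiplying by 1.20 gives 144 per group, or 288 entrants, which does not match either. With the reported enrolment, 240 remaining would mean dropout of 1 − 240/258 = 7.0% or 1 − 240/259 = 7.3%. Since 206 to 207 is below 240, no allocation ratio leaves 120 in both groups.

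**3. What the sample can detect.** The smallest detectable d at 80% power is approximately (1.96 + 0.84) × √(2/n). The t-test version is tabulated, with d × 452.8 giving MET-min/week.

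| n per group | Detectable d | MET-min/week | Power at d = 0.2 | Power at d = 0.3 | Power at d = 0.552 |
|---|---|---|---|---|---|
| 103 (completers) | 0.39 | 178 | 30% | 57% | 98% |
| 120 (as stated) | 0.36 | 164 | 34% | 64% | 99% |
| 129 (all entrants, 258/2) | 0.35 | 159 | 36% | 67% | 99% |

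Detecting d = 0.2 with 80% power would need 394 per group.

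**4. Baseline imputation.** The last row ignores the dilution that imputation causes. As an illustration, suppose 20% are missing at random in each group and are assigned zero change. The difference becomes 0.8 × 250 = 200. The variances are 0.8 × 500² + 0.16 × 300² = 214,400 and 0.8 × 400² + 0.16 × 50² = 128,400, so the pooled SD is √171,400 = 414 and d = 200/414 = 0.483. With 129 per group, power is about Φ(0.483 × √64.5 − 1.96) = Φ(1.92), or 97%.

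**5. Associations.** With 206 women, power for the article's moderate correlation of 0.22 is Φ(atanh(0.22) × √203 − 1.96), or about 89%.

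**The case against.** The strongest reply is that nothing of substance depends on the figure. About 103 per group is roughly twice the 52 the article requires for PA and well above its figure of about 60, and power is about 95% even at an effect of 0.5. The default analysis keeps all entrants, so 103 describes only the completers. The one-woman discrepancy moves the retained number only from 103.2 to 103.6 per group. All of this stands, and it makes the point minor. It does not remove the contradiction among the three stated figures. A planned enrolment of 300 might explain the 120, but the article mentions none.

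A reader might also infer that the sensitivity claim is simply false, because neither 103 nor 120 per group has adequate power for a small effect. The article does not support that. The inference depends on d = 0.2, a convention the article never adopts. The only scale it sets out is for associations, and that starts at moderate (5% of variance, r = 0.22, about d = 0.45). The detectable d of 0.36 to 0.39 lies below both that level and the planned 0.56, so the phrase is defensible if small means smaller than planned. What stands is that the wording is unquantified and would fail if the conventional meaning was intended.

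Nor do the documents say how a null PA result would be interpreted, so a forecast that it would be taken to exclude small effects is conjecture.

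**Conclusion.** The point holds as a minor correction of a stated figure. The 120 per group is inconsistent with 20% dropout from 258 or 259 entrants, and that conclusion needs no assumption about allocation. The size of the error, about 17 women per group (120 against 103), does assume 1:1 allocation. The entry count must be given one value. The phrase about small PA differences should be quantified, but it is not shown to be false.

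The trial is not underpowered for the effects it was planned on. Power for the assumed PA difference is about 98% in completers, and about 97% with baseline imputation under the simple missing-at-random illustration above. No design feature, endpoint or analysis has to change.

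**What to change.** In Sample size and power:

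- Replace 120 per group with about 103 completers per group at 1 year, marked as assuming equal allocation (or use the actual group sizes). Add that the intent-to-treat analysis with baseline imputation keeps all entrants, about 129 per group.
- Replace the phrase about small PA differences with the detectable difference: 80% power for d of about 0.39 (about 178 MET-min/week) in completers, and about 98% power for the assumed 250 MET-min/week. If the intent-to-treat figure is also quoted, say that imputing baseline values shrinks the expected difference.

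In Study design and Inclusion criteria, reconcile 259 with 258 and use one number as the intent-to-treat denominator.

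The cost is a text correction. The stated retention and sensitivity become slightly less favourable, and nothing in the conduct of the trial changes.

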## Discussion

Despite the cumulative evidence for the positive role of regular physical activity and exercise in long-term weight management, it remains unclear why only about 20% of individuals seeking weight loss are able to successfully integrate activity behaviors into their lifestyles and achieve long-lasting weight control [6]. Since few data are available concerning exercise motivation in the context of weight control, studies in this domain are critical and we believe further application of SDT in the behavioral treatment of obesity is a potentially fruitful area to explore. On the other hand, although empirical data generally support the efficacy of research using motivational techniques, the underlying mechanisms for change remain largely unexplored. According to Bauman [67], if an intervention is not well implemented, it may not affect the proposed mediators and, as a consequence, outcomes may not be sufficiently improved. According to previous research [18,20,30], SDT should be useful in explaining the dynamics of motivation during the course of obesity treatment, providing direct empirical support for autonomy, competence, and perceived autonomy support as three of the psychological processes through which intensive behavioral treatment might operate.

Key innovative features of this study are: a theory-based intervention based on the principles of Self-Determination Theory, a unique setting and population (the first long-term RCT for weight loss conducted in Portugal), *a priori *selection of putative moderators and mediators responsible for therapeutic change, high emphasis on physical activity/exercise, both as exposure and outcome, a systematic evaluation of a large range of potential determinants of outcomes, objective measurements of physical activity (via accelerometry), and precise measure of body composition changes (via DXA).

Results from this study are expected to contribute to a better understanding of how motivational characteristics, particularly those related to physical activity/exercise, influence treatment success during obesity treatment, while exploring the utility of Self-Determination Theory for promoting health behavior change in this most important context. That theory should evolve based on rigorous empirical evidence and that applied intervention research is one of the best ways to evaluate and refine theory [31].
